### Research objectives and hypothesis

The purpose of this study is twofold: first, to determine the effectiveness of four mixed modalities, namely Mixed ABC, A + B, C + A, and B + C, of three training programs (A: cognitive training, B: physical training, and C: combined cognitive and physical training (CCPT)) on cognition, fitness, and psychosocial-related health of community-dwelling older adults in Hong Kong; and second, to determine which specific training program being most effective among the three programs as compared to the control group (CG).

The hypothesis is that participants with the integrated format of three training modes will have higher cognition and fitness scores than the participants with the other combinations of two training modes, and all these mixed modalities will show greater positive outcomes than the control group.

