## Methods

### Research design

This study is a cluster randomized controlled trial (CRCT), to be carried out in 20 community elderly centres (see Fig. 1). The elderly centres will be randomly selected from the population list of elderly service providers in the 18 districts of Hong Kong and assigned to either one of the 4 Intervention Groups (IGs) or the Control Group (CG). There will be 16 centres in the IGs and 4 centres in the CG participating in a 6-months program (4-month intervention with 2-month follow-up). The 20 participating centres will be equally allocated to two Phases, I and II, with each Phase involving 8 centres in IGs and 2 centres in CG. Each IG will be randomly assigned to one of the four combinations of three training modes that include cognitive (A), physical (B), and combined cognitive and physical training (CCPT, i.e. C), namely Mixed ABC, A + B, C + A, B + C. The intervention will last for 4 months in which the training is conducted for 16 sessions, 2 sessions per week, and 60 min per session.

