### Statistical analysis plan

Data analysis will be performed using the Statistical Package for social sciences (IBM SPSS ver. 27). All data points that were considered outliers, which are out of the interquartile range (IQR) covering the 50% central of samples, will be excluded from analyses. For analyzing program effects, a mixed-effects ANOVA will be used. In this model, there will be a between-subjects factor consisting of five groups (CGs = 0, IGs = 1 to 4) and a within-subject factor consisting of four Trials (Time = 1 to 4). The dependent variables will be the outcome measures of the three cognitive tests and the five physical fitness tests. The independent variables will be time (1 pre-test, 2 post-tests, and 1 follow-up) and intervention (IGs with 4 combinations of training modes & CGs). The participating elderly centre as a cluster will be treated as a random effect. Assumptions (normality, sphericity, etc.) for mixed-effects ANOVA will be tested using an alpha level set as 0.05. The focus of this mixed-effects ANOVA will be mainly on the between-group differences, i.e., the differences among the four IGs. Post-hoc comparisons among IGs will be conducted with Bonferroni correction after finding significant effects. Next, for analyzing specific intervention effects in the 3 treatments crossover design, a similar mixed-effects ANOVA will be used. In this second model, there will be one within-subject factor of four repeated trials (Time = 1 to 4). The dependent variables will be the outcome measures of the three cognitive tests and the four physical fitness tests. The independent variables of time (pre-test, 2 post-tests, and follow-up) and three training modes will be examined by ANOVA with repeated measures. The focus of the second model is to examine the individual effect of the three training modes, so a pre-planned contrast will be conducted to examine their effects. Based on these statistical analyses, results and conclusions will be drawn.

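### The comparison of each training combination with control has no planned test, and the between-group focus does not match the group-by-time test that reproduces the sample size

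*Protocol article*

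**What the plan says.** Research objectives and hypothesis states a hypothesis in two parts. The first ranks Mixed ABC above the two-mode arms: "participants with the integrated format of three training modes will have higher cognition and fitness scores than the participants with the other combinations". The second is that "all these mixed modalities will show greater positive outcomes than the control group". The second objective in the same section is to find the most effective of the three training programmes, again with the control group as the reference.

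Statistical analysis plan describes two models.

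- **Model 1.** "there will be a between-subjects factor consisting of five groups", with control coded 0 and the four combinations coded 1 to 4, crossed with four time points of which the first is the pre-test. On its purpose: "The focus of this mixed-effects ANOVA will be mainly on the between-group differences, i.e., the differences among the four IGs". On follow-up tests: "Post-hoc comparisons among IGs will be conducted with Bonferroni correction after finding significant effects".
- **Model 2.** A repeated-measures ANOVA on time and the three training modes, with one pre-planned contrast on the effects of those modes. The control group is not mentioned.

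Neither model names the group-by-time interaction or an adjustment for the pre-test. On clustering the section says: "The participating elderly centre as a cluster will be treated as a random effect". Sample size gives a repeated-measures ANOVA of 4 trials by 5 groups with effect size 0.175, alpha 0.05, power 0.90 and rho 0.5. The result is 95 unclustered, 228 after a design effect of 2.4, and 285 after 20% attrition.

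**The concern.** Four of the 20 centres are allocated to control so that the programmes can be shown to work. Every outcome is measured four times on the same people, so some improvement from practice is plausible in every arm. Only a comparison with control separates that from an effect of training. If the analysis follows the stated focus, the main report could rank the combinations against one another and still contain no planned comparison showing that any of them beats no intervention.

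The second issue is which effect is tested. The pre-test precedes training, so randomised groups should not differ there except by chance, and with four centres per arm chance differences can be sizeable. A between-group effect taken over all four time points includes that assessment. It dilutes any training effect and adds noise. The effect of training lies in the difference between groups in change over time, or in post-test scores adjusted for the pre-test.

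**Working it through.** **1. Hypotheses against planned comparisons**

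| Claim in Research objectives and hypothesis | Comparisons needed | Planned in Statistical analysis plan |
|---|---|---|
| Mixed ABC better than each two-mode arm | 3 | Yes, within the 6 post-hoc pairs among the four intervention groups |
| Each combination better than control | 4 | None named |
| Training programmes compared with control (second objective) | 3 modes against control | Contrast on the modes only; control not mentioned |

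The five-group omnibus test does include control. A significant result says only that some difference exists among five means. It may come entirely from differences among the intervention groups.

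**2. Which test the sample size belongs to**

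Inputs from Sample size: f = 0.175 (f² = 0.030625), alpha 0.05, power 0.90, rho = 0.5, k = 5 groups, m = 4 times. The noncentral F formulas for a repeated-measures ANOVA are:

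- Interaction: λ = f²·N·m/(1 − rho), df = (k − 1)(m − 1) and (N − k)(m − 1)
- Within factor: same λ, df = m − 1 and (N − k)(m − 1)
- Between factor: λ = f²·N·m/(1 + (m − 1)·rho), df = k − 1 and N − k

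| Test | Smallest N for 0.90 | λ at N = 95 | df at N = 95 | Power at N = 95 |
|---|---|---|---|---|
| Group-by-time interaction | 93, or 95 in five equal groups | 0.030625 × 95 × 4/0.5 = 23.275 | 12, 270 | 0.909 |
| Within factor (time) | 60 | 23.275 | 3, 270 | 0.988 |
| Between factor (group) | 320 | 0.030625 × 95 × 4/2.5 = 4.655 | 4, 90 | 0.352 |

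Only the interaction reproduces 95. The remaining steps also reproduce: design effect 1 + 14 × 0.1 = 2.4; 95 × 2.4 = 228; 228/0.8 = 285. Carrying the between-group effect through the same steps gives 320 × 2.4 = 768 and 768/0.8 = 960. These figures take 0.175 as the size of whichever effect is tested.

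**3. What averaging in the pre-test costs**

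Assumptions: a constant difference d at T2, T3 and T4, none at T1; equal correlation 0.5 between times; unit variance; clustering ignored.

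| Summary compared between two groups | Difference | Variance per person | Signal (difference/√variance) |
|---|---|---|---|
| Mean of T1 to T4 | 0.75d | (1 + 3 × 0.5)/4 = 0.625 | 0.949d |
| Mean of T2 to T4 | d | (1 + 2 × 0.5)/3 = 0.667 | 1.225d |
| Mean of T2 to T4 minus T1 | d | 0.667 + 1 − 2 × 0.5 = 0.667 | 1.225d |
| Mean of T2 to T4 adjusted for T1 | d | 0.667 − 0.5² = 0.417 | 1.549d |

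Information kept by the T1 to T4 mean: (0.949/1.549)² = 0.375 against the adjusted mean, and (0.949/1.225)² = 0.60 against the post-only or change mean.

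**4. What the control contrasts can detect**

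Effective sample per arm is 228/5/2.4 = 19. For the adjusted T2 to T4 mean, with Bonferroni over four contrasts (0.05/4 = 0.0125), the normal approximation gives power of 0.46 at d = 0.5 and 0.91 at d = 0.8. The values of d are illustrative. The approximation is optimistic, because four centres per arm leave few degrees of freedom, and it carries the design effect of 2.4 over to the adjusted mean.

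**The case against.** The strongest reply is that the section is a short summary and never says the group main effect is the test. The model has a time factor, and both the phrase about between-group differences and the one about significant effects could cover the interaction. The sample size points that way. This stands in part: averaging in the pre-test is the plain reading, not an explicit statement. But the interaction is not named anywhere, so the two sections still need to be reconciled.

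It can also be said that control is a level of the group factor and that the focus is described as mainly, not only, on the intervention groups. That is true, and the omnibus test does use control. It does not supply the four comparisons that the hypothesis asserts. Nor is this a detail left to a fuller plan, because the article states which comparisons will follow and confines them to the intervention groups.

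A reader might infer three stronger things that the document does not support:

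- That the trial's hypothesis as a whole goes untested. The Mixed ABC half is covered by the planned post-hoc comparisons.
- That the analysis will have a particular inflated type I error for group-by-time because centre is the only random effect named. The article does not give the form of that effect and gives no centre-by-time variance, so any rate would rest on assumed values.
- That chance differences at the pre-test bias the comparison. Under randomisation they add variance, not bias.

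Finally, 37.5% uses the most favourable comparator. Against a post-only or change score the figure is 60%, and both depend on a constant effect after T1.

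**Conclusion.** The concern holds in a limited form. No comparison of any combination with control is planned in either model, although superiority to control is half of the hypothesis and control is the reference in the second objective. This follows from the text alone and needs no assumption.

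The among-combination half is tested, but the effect is not clearly defined. Read plainly, it is a four-time average that recovers 75% of a constant post-training difference, with the loss of information worked out above (rho 0.5, clustering ignored). That reading also conflicts with the sample size: the stated 0.90 power belongs to the omnibus group-by-time interaction, and the same inputs give about 0.35 for the between-group effect.

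This should be corrected before the data are analysed, because control contrasts chosen after seeing the results would carry less weight.

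**What to change.** In Statistical analysis plan:

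1. Name the primary test as group-by-time, or as post-test scores adjusted for the pre-test.
2. Pre-specify two families of contrasts: each of the four combinations against control, and Mixed ABC against the three two-mode arms. State the multiplicity control. Bonferroni would give 0.05/4 = 0.0125 for the control contrasts alone, or 0.05/7 = 0.0071 over all seven.
3. State how control enters model 2, so that the second objective has a matching comparison.
4. Use an error term for these contrasts that reflects variation between centres in change over time. A centre intercept alone cancels out of group-by-time.

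The choice of a single primary time point, the particular multiplicity procedure, a term for Phase and the degrees-of-freedom method are options for the authors, not corrections.

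The cost is analysis wording, with no new data. The downside is power: single contrasts of four centres against four, at a corrected alpha, have less power than the omnibus test used for sizing. Sample size should therefore say that the stated 0.90 applies to the omnibus interaction only, and should report what difference from control the planned contrasts can detect.

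### The hypothesis that Mixed ABC beats the two-mode combinations has no test of its own in model 1; a planned contrast would match it better and, for many effect patterns, with more power

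*Protocol article*

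**What the plan says.** Under Research objectives and hypothesis, the protocol article predicts an order among the arms: "participants with the integrated format of three training modes will have higher cognition and fitness scores than the participants with the other combinations", meaning those built from two modes. It adds that "all these mixed modalities will show greater positive outcomes than the control group".

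Under Statistical analysis plan, the first model is a mixed-effects ANOVA with "a between-subjects factor consisting of five groups (CGs = 0, IGs = 1 to 4"). The repeated assessments enter as "a within-subject factor consisting of four Trials (Time = 1 to 4"), and centre is a random effect. Its stated focus is the differences among the four intervention groups (IGs). The follow-up is fixed as: "Post-hoc comparisons among IGs will be conducted with Bonferroni correction after finding significant effects". No contrast of Mixed ABC with the two-mode arms is named.

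The section does name a planned contrast, but only for the second model, which looks at the three single training modes: "so a pre-planned contrast will be conducted to examine their effects".

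**The concern.** The first limb of the hypothesis is one directed comparison. The procedure chosen for it is an undirected gate followed by unordered pairs. This has three consequences.

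- The gate does not answer the question. A five-group effect can be significant because control differs from the IGs, or because two-mode arms differ from one another.
- The comparison of interest is split into three of six pairs. The other three (A + B vs B + C, A + B vs C + A, B + C vs C + A) say nothing about three modes against two, yet they take half of the Bonferroni correction.
- The three Mixed ABC pairs can disagree, and the text does not say which pattern would support the hypothesis.

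At stake is the chance of detecting a real advantage of Mixed ABC, and having a single estimate with an interval to report for it.

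**Working it through.** **The plan's own sample size.** Sample size section: f = 0.175, alpha 0.05, power 0.90, rho 0.5, 5 groups, 4 time points. For the group-by-time interaction, λ = f² × N × 4/(1 − rho) = 0.030625 × 95 × 8 = 23.3, with df 12 and (95 − 5) × 3 = 270. Power is 0.909; the smallest N is 93, or 95 in five equal groups. Design effect 1 + 14 × 0.1 = 2.4; 95 × 2.4 = 228; 228/0.8 = 285. The figures reproduce. They power the interaction across all five groups, not the comparison of Mixed ABC with the two-mode arms.

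**Inputs for the comparison.** From the document: 4 centres per arm, ICC 0.1, and 228/20 = 11.4 analysed per centre. Assumed: SD 1 for the analysed score, centre-level error df of 20 − 5 = 15, and two-mode arms equal to each other and to control.

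**Precision.**
- Variance of a centre mean: 0.1 + 0.9/11.4 = 0.1789. Variance of an arm mean: 0.1789/4 = 0.0447.
- Contrast (Mixed ABC minus the mean of three arms): SE = √(0.0447 × (1 + 1/3)) = 0.244. Critical t at two-sided 0.05 is 2.131, so an observed difference of about 0.52 SD is needed.
- One pair: SE = √(2 × 0.0447) = 0.299. Critical t at 0.05/6 is 3.036, so about 0.91 SD is needed.

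For 0.5/0.6/0.75 SD the contrast's noncentrality is 2.05/2.46/3.07.

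**Power** (contrast agrees with the noncentral t; the plan's route is simulated on centre means, 100,000 or more trials per scenario):

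| Mixed ABC advantage | 0.5 SD | 0.6 SD | 0.75 SD |
|---|---|---|---|
| Planned contrast | 48.2% | 63.2% | 81.9% |
| Plan: five-group F, then at least one Mixed ABC pair | 21.6% | 32.2% | 51.4% |
| Difference (points) | 26.6 | 31.0 | 30.5 |
| Plan: all three Mixed ABC pairs | 3.1% | 6.2% | 15.1% |

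**Variations on the plan's route (at least one pair).**
- F over the four IGs only: 24/35/54%.
- Control 0.5 SD below the two-mode arms, so the gate matters little: 24/35/55%.
- ICC 0.05: 30/44/66%, against 60/76/91% for the contrast.
- Mixed ABC equal to A + B and 0.75 SD above the other two: the mean difference is 0.75 − 0.75/3 = 0.5 SD, so the contrast has 48%; the plan has 47%.
- The protocol's own f = 0.175 and effective N of 95: losses of 2 to 27 points, depending on the effect tested, the df and the control mean.

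**What the gate responds to.** With Mixed ABC equal to every two-mode arm and all IGs 0.75 SD above control, the five-group F rejects 57% of the time and the contrast 5%. With two-mode arms at −0.5/0/+0.5 SD and Mixed ABC at their mean, the figures are 62% and 5%.

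**Time.** Weights on groups alone would average the pre-test into the effect. An advantage of 0.75 SD at T2–T4 and none at T1 becomes 0.75 × 3/4 = 0.56 SD, and contrast power falls from 82% to 58%. The contrast must therefore be defined on change from T1.

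**The case against.** An omnibus test with corrected post-hoc pairs is standard and valid, and the article's first purpose covers all four combinations, so the remaining three pairs serve a stated aim. That stands: they belong in the report, though not in the correction for this hypothesis. The F is only a gate, so its rejecting for other reasons does not by itself produce a false claim about Mixed ABC.

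The strongest point concerns the wording. Higher than the other combinations can be read as higher than each, and a contrast against their average can be positive when Mixed ABC does not beat every arm. In the scenario above where it equals A + B, the contrast is positive 48% of the time. This also stands, and it limits what the contrast may be said to show. It does not rescue the present route: if superiority to each arm is meant, three planned tests at 0.05 that must all succeed have 14/24/42% power for 0.5/0.6/0.75 SD with equal two-mode arms, against 3/6/15% for the plan.

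It can also be said that contrast coefficients are usually left to a fuller plan. Here, however, the article fixes the procedure for model 1 and reserves a planned contrast for model 2.

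A reader might infer a fixed loss of 24 to 31 points of power. The documents do not support that: they give neither the effect pattern nor the definition of success on which the figure depends. A reader might also infer inflated false-positive error; the Bonferroni step controls it for these pairs.

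Separately, the post-hoc step covers IGs only, so the hypothesis against control has no named follow-up comparison. The contrast proposed here does not address that.

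**Conclusion.** The point holds as a cheap improvement. Model 1 contains no test whose null is that Mixed ABC equals the two-mode combinations, although that is the first limb of the stated hypothesis. The analysis is valid but fits its hypothesis poorly.

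The size is conditional. With 4 centres per arm, 11.4 analysed per centre, ICC 0.1, 15 error df, SD 1 and two-mode arms equal to each other and to control, the plan gives up about 27 to 31 points of power for advantages of 0.5 to 0.75 SD, counting any one significant Mixed ABC pair as success. Equal two-mode arms favour the contrast; when Mixed ABC equals one of them, the gain almost disappears. A stricter definition of success, such as all three pairs, makes the plan's shortfall larger.

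**What to change.** In model 1, pre-specify a contrast on change from T1, that is, a group-by-time contrast at one named post-test: Mixed ABC minus the mean of A + B, B + C and C + A (weights 1, −1/3, −1/3, −1/3, and 0 for control). Test it two-sided at 0.05 with centre-level degrees of freedom, without requiring a significant omnibus F, and report the estimate with its 95% CI.

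State that it supports only the claim that Mixed ABC is better than the two-mode average. Report the three Mixed ABC pairwise differences beside it, corrected for three comparisons rather than six. If the sponsor means better than each, make those three planned comparisons the test instead and say so. Keep the other IG pairs as secondary description.

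The cost is a few sentences and one contrast statement in the software, with no new data or participants. The downside is that the contrast alone does not show which two-mode arm is beaten, and it can be positive when Mixed ABC does not beat every one.

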### Interventions

Each selected elderly centre will be randomly assigned to either IGs or CG and asked to help to recruit participants with a sample size of 14–15 older adults. There will be 16 centres in the IGs to receive four combinations of three training modes (A: cognitive training only, B: physical training only, C: CCPT) and with 4 centres in IGs. The four types of combinations are 1. Mixed ABC, 2. A + B, 3. B + C, 4. C + A, matched with 4 CGs in total. For the case of combination 1. Mixed ABC, participants will receive different training modes every 2 consecutive weeks with randomized order. For the case of combinations 2, 3, and 4, the participants’ centres will receive an assigned sequential order of two training modes with each mode lasting for 2 months. All participants of IGs will attend training sessions twice a week, and 60 min duration per session (per mode). The random allocation sequence of intervention was generated by a blinded statistician external to the research team. Due to the nature of each intervention, blinding cannot be applied to the participants, while the blinded group allocation will be applied to the data assessors and analysts. Each subject will be identified by the number code. Data from those participants having more than 70% attendance will be analyzed. No further follow-up with missing cases will be done because they will be usually missing at random (such as absences due to doctor’s appointments or being sick).

The three training modes (A, B, and C) are introduced as follows:A: Cognitive training only

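### The second (mode-specific) model is treated as a three-treatment crossover, but it leaves out the control group and any carry-over term, so it cannot give each mode's effect against control

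*Protocol article*

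**What the plan says.** All references are to the protocol article.

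- **Objective** (Research objectives and hypothesis). The second aim is "to determine which specific training program being most effective among the three programs as compared to the control group (CG").
- **Second model** (Statistical analysis plan). "for analyzing specific intervention effects in the 3 treatments crossover design, a similar mixed-effects ANOVA will be used". It goes on: "In this second model, there will be one within-subject factor of four repeated trials (Time = 1 to 4"), and "The independent variables of time (pre-test, 2 post-tests, and follow-up) and three training modes will be examined by ANOVA with repeated measures". Its purpose is stated: "The focus of the second model is to examine the individual effect of the three training modes", through a pre-planned contrast.
- **First model** (same section). This one has "a between-subjects factor consisting of five groups (CGs = 0, IGs = 1 to 4"). Control appears as a level here and is not named for the second model.
- **Delivery of the modes** (Interventions). In the three two-mode combinations, centres "will receive an assigned sequential order of two training modes with each mode lasting for 2 months". In Mixed ABC, "participants will receive different training modes every 2 consecutive weeks with randomized order".
- **Assessments** (Research design). T2 comes directly after month 2, T3 directly after month 4, and T4 two months after training has ended. Control participants take all four assessments without training.

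A smaller inconsistency sits in the same paragraph: the first model lists five fitness tests, the second lists four, and the Outcome measures section describes five.

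**The concern.** A crossover analysis credits the outcome in each period to the treatment given in that period. This needs every visit to map to one treatment, earlier treatments to have worn off or be modelled, and a reference that removes period effects such as practice on repeated tests. The second model, as described, meets none of these fully.

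- Two modes of 2 months each fill the 4-month intervention and T2 falls at the switch, so there is no room for a washout.
- Mixed ABC participants do receive all three modes, but assessments 2 months apart cannot separate modes that change every 2 weeks.
- T4 is included in the time factor although no mode is being given then.
- The comparison that the objective asks for, mode against control, has no control level.

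At stake is the second of the two stated objectives. Practice gain could be reported as a training effect, and the ranking of A, B and C could partly reflect which mode came before which.

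**Working it through.** **1. The plan's own figure.** The Sample size section gives effect size f = 0.175, alpha 0.05, power 0.90, rho 0.5, 5 groups and 4 times. For the group-by-time interaction:

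- λ = f²·N·m/(1 − rho) = 0.175² × 95 × 4 / 0.5 = 23.3; df = 12 and 270; power at N = 95 is 0.909. The minimum is 93, and 95 is the next multiple of 5.
- Design effect 1 + (15 − 1) × 0.1 = 2.4; 95 × 2.4 = 228; 228/0.8 = 285.

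The 285 reproduces. It is sized on the five-group layout; no figure is given for the second model.

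**2. Can a single mode's effect be estimated?** Take the changes T1–T2 and T2–T3 in the two-mode arms, with two period terms and three mode terms. Every participant is in exactly one mode in each period, so period 1 + period 2 = A + B + C.

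| Terms | Control included? | Rank | Single-mode effect | A minus B |
|---|---|---|---|---|
| period, mode | no | 4 of 5 | not estimable | estimable |
| period, mode | yes | 5 of 5 | estimable | estimable |
| period, mode, carry-over | yes | 8 of 8 | estimable | estimable |

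The same ranks arise for orders A-B, B-C, C-A and for all six orders.

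**3. Practice (assumed 0.2 SD, then 0.1 SD; the article gives no figure).** If change is credited to the mode being given, each mode gains (0.2 + 0.1)/2 = 0.15 SD with no true effect. With control in the model this becomes 0. In A-B, B-C, C-A each mode occurs once per period, so common practice cancels from every mode-versus-mode contrast.

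**4. Carry-over (assumed: 0.2 SD extra change from T2 to T3 after A, none after B or C, all mode effects zero).** In A-B, B-C, C-A only the second period of A-B is affected.

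- Period and mode terms: B averages (0 + 0.2)/2 = 0.10, and A and C average 0, so A minus B = −0.10 SD.
- With sequence effects added, only T2–T3 minus T1–T2 differences count. Let π be the period-2 minus period-1 effect: π + (B − A) = 0.2; π + (C − B) = 0; π + (A − C) = 0. Summing gives π = 0.2/3 = 0.067, so A minus B = −0.13 SD.
- With all six orders the shift is −0.05 SD, or −0.10 SD with sequence effects.

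**5. Dependence on coding.** Let tA, tB, tC be the mode effects and k the share of the first mode's effect retained at T3. Compare order A-B with order C-A at T3, as B minus A:

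- T3 level: (tB + k·tA) − (tA + k·tC) = (tB − tA) + k(tA − tC).
- T2–T3 change: (tB − tA) + (k − 1)(tA − tC).

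With assumed tA = tB = 0.2 and tC = 0.4, the true difference is 0:

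| k | T3 level | T2–T3 change |
|---|---|---|
| 1 | 1 × (−0.2) = −0.2 | 0 × (−0.2) = 0 |
| 0.5 | 0.5 × (−0.2) = −0.1 | −0.5 × (−0.2) = +0.1 |

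When tA and tC differ, level coding is unbiased only at k = 0 and change coding only at k = 1. The article states neither the coding nor the orders.

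**The case against.** The strongest reply is that a condensed article need not spell out contrast coding, sequence terms or carry-over terms, and that the model is called similar to the first, which includes control. Control data are collected at all four visits. The stated hypothesis concerns combinations against each other and against control; the first model answers that, and the sample size rests on it.

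Much of this is right. The hypothesis, the first model and the 285 are untouched. It does not rescue the second model, because the article does list its independent variables and control is not among them. Importing the five-group factor would not help either: those groups are combinations, not modes, and carry-over would remain unmodelled.

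Three stronger readings are tempting and are not supported:

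- *That practice confounds every comparison of modes.* Time is in the model as well as mode, and common practice cancels when each mode occurs once per period.
- *That carry-over is completely inseparable from mode.* This could hold only within T3, and only if orders follow the combination names. The article says just that an order is assigned, and with 4 centres per combination counterbalancing is not excluded. T1–T2 change is free of carry-over.
- *That a definite bias follows, such as B looking 0.2 SD worse than A.* That comes from one contrast of T3 levels that the article never specifies; on change scores the same inputs give 0.

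**Conclusion.** The point holds in limited form. Followed as described, the second model cannot give the effect of A, B or C against control, and this does not depend on any assumed effect size. It follows from the listed variables and from every two-mode participant being in some mode at T2 and at T3.

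The carry-over bias in mode contrasts at T3 is real in kind, but its size and sign are unknown. The shifts of 0.10 to 0.13 SD (listed order) and 0.05 to 0.10 SD (all six orders) rest on an assumed 0.2 SD carry-over from A alone; the practice figure of 0.15 SD is likewise an illustration. The trial itself does have a control group: the gap is in this model only, and the data to close it are already being collected.

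**What to change.** Revise the second-model paragraph as follows.

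- Drop the crossover label and include control as the reference level.
- Make the primary single-mode analysis the T1–T2 change by first-assigned mode against control, adjusted for T1 and Phase, with centre as a random effect.
- Exclude Mixed ABC and T4 from single-mode attribution.
- Report T3 as a sequence effect, or use it in a supportive model with time-varying mode, period and carry-over terms and with control included. Do not also add fixed sequence effects under orders A-B, B-C, C-A: the rank then falls to 8 of 12, and neither a single-mode effect nor A minus B is estimable.
- List the same five fitness tests in both models.
- If the order within combinations is not yet fixed, balance it across centres. The Interventions section describes the allocation sequence as already generated, so this may come too late; the analysis changes do not depend on it.

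**Cost.** The analysis changes are wording and need no new data. The price is precision and scope: the mode effect covers only the first 2 months. If orders are cyclic or balanced, 12 two-mode centres give 4 per mode: 4 × 285/20 = 57 enrolled, 57 × 0.8 = 45.6 after attrition, and 45.6/2.4 = 19 effective participants. Against a control group of the same size, the detectable unadjusted difference at 80% power and two-sided 0.05 is about (1.96 + 0.84) × √(2/19) ≈ 0.9 SD, before any allowance for having only 8 centres in the comparison. Adjustment for T1 should improve on this. Discarding T3 entirely is therefore a debatable trade-off, which is why it is kept in a supportive role. The low precision should be stated in the plan.
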